# CELPI: trial protocol for a randomised controlled trial of a Carer End of Life Planning Intervention in people dying with dementia

**DOI:** 10.1186/s12877-022-03534-1

**Published:** 2022-11-16

**Keywords:** Dementia, Palliative care, Person-centred care, Randomised controlled trial, Emergency medicine

## Abstract

**Background:**

Dementia is a leading cause of death in developed nations. Despite an often distressing and symptom laden end of life, there are systematic barriers to accessing palliative care in older people dying of dementia. Evidence exists that 70% of people living with severe dementia attend an emergency department (ED) in their last year of life. The aim of this trial is to test whether a Carer End of Life Planning Intervention (CELPI), co-designed by consumers, clinicians and content specialists, improves access to end of life care for older people with severe dementia, using an ED visit as a catalyst for recognising unmet needs and specialist palliative care referral where indicated.

**Methods:**

A randomised controlled trial (RCT) enrolling at six EDs across three states in Australia will be conducted, enrolling four hundred and forty dyads comprising a person with severe dementia aged ≥ 65 years, and their primary carer.

Participants will be randomly allocated to CELPI or the control group. CELPI incorporates a structured carer needs assessment and referral to specialist palliative care services where indicated by patient symptom burden and needs assessment. The primary outcome measure is death of the person with dementia in the carer-nominated preferred location. Secondary outcomes include carer reported quality of life of the person dying of dementia, hospital bed day occupancy in the last 12 months of life, and carer stress. An economic evaluation from the perspective of a health funder will be conducted.

**Discussion:**

CELPI seeks to support carers and provide optimal end of life care for the person dying of dementia. This trial will provide high level evidence as to the clinical and cost effectiveness of this intervention.

**Trial registration:**

ACTRN12622000611729 registered 22/04/2022.

**Supplementary Information:**

The online version contains supplementary material available at 10.1186/s12877-022-03534-1.

## Background

One in every four people who reach the age of 65 will die of or with dementia, yet death from dementia is “under-recognised and stigmatised” [1]. In people with advanced dementia, the final year of life is characterised by a trajectory of progressive severe disability and health problems such as pain, pressure injury, infections, eating difficulties and changed behaviours [2, 3]. The physical symptoms are not dissimilar to those experienced by people with terminal cancer. However, compared to the relatively well established link between terminal cancer and specialist palliation, referral pathways to access palliative care for the population dying of advanced dementia, and what that palliative care looks like, are disorganised and difficult to qualify [4].

Barriers to the uptake of palliative care include lack of understanding of the disease trajectory of advanced dementia (with only one third of family carers understanding that severe dementia is a terminal illness) [5]; a lack of responsibility for initiation of the process; and misapprehension that end of life planning is synonymous with withholding essential treatment [6]. Palliative care in people with advanced dementia is further undermined by i) a lack of fully validated symptom scales that can identify the range of cognitive, physiological, emotional and behavioural symptoms occurring in late-stage dementia; ii) incomplete information available about the healthcare and lifestyle preferences and values of a person who lacks capacity to communicate these; and iii) the frequent involvement of different medical specialties, who may focus on individual diseases or organ systems and not recognise that the person is approaching the end of their life, or is now dying.

Over 70% of people dying of and with dementia attend an emergency department (ED) at least once in their last 12 months of life, with the highest rates in those with other comorbidities and living with a carer at home [7]. This raises the opportunity of using the ED visit as a "teachable moment", helping bridge the gap between the sometimes-abstract aspects of care planning and the realities of acute illness. Using the ED visit as the launching pad to initiate an intervention that will improve end of life care for people with severe dementia would invert the usual negative experiences of an ED, where the expectations of dementia-friendly care are almost never met [8].

The objective of this randomised controlled trial (RCT) is to investigate the impact of a Carer End of Life Planning Intervention (CELPI) to determine whether this results in a meaningful improvement in outcomes for people with severe dementia approaching end of life who attend an ED, and their carers.

## Methods

### Design

A single-blind multi-centre parallel RCT of CELPI compared to usual post-discharge care will be conducted (Fig. 1).

**Fig. 1 Fig1:**
[figure not shown]
Participant flow

### Participants and setting

We will enrol dyads of a person with dementia and their carer, with the carer as determined by relevant state legislation. People with dementia aged at least 65 years old attending one of six enrolling EDs will be screened after attendance for trial inclusion and exclusion criteria. The EDs are all metropolitan tertiary referral EDs located in Melbourne, Perth and Sydney, Australia.

#### Inclusion Criteria

The person with dementia must have ALL of the following:Established prior documented diagnosis of dementia, supported by an appropriate assessment screen e.g. mini mental state exam (MMSE) [9]. or Montreal Cognitive Assessment (MoCA) < 13/30Functional Assessment Staging Test (FAST) Stage 6d-7f [10].A carer residing within a 30 km travel distance of the enrolling ED or, if beyond that radius, agreeable to using telehealth to undertake the intervention.Medicare eligible

##### Exclusion Criteria:

No identifiable singular adult carer as a surrogate medical decision makerPerson with dementia is under the care of the Public GuardianClinician judgement that death is imminent (within one week)Person with dementia is a current patient of a specialist palliative care service, or a prior patient within the preceding 12 months.Significant symptoms (e.g. pain, dyspnoea) requiring a referral to specialist palliative care on this presentation.Carer requires translation of written and spoken language

People with dementia will be eligible to participate in this RCT if they reside in residential aged care or the community, and if they are discharged home from the ED or admitted to an inpatient ward.

### Sample size

The study is powered to detect a significant difference in the primary outcome of death within the follow up period in the carer supported preferred location. Where the person with dementia has previously indicated a preferred location, this will be ascertained from and confirmed with the carer. Otherwise, the carer will be requested to nominate. Whilst there are large datasets that describe the location of death of people with advanced dementia, only two small studies from a recent systematic review provided data on preferred location of death [11].

Using this review to assume 60% of people with dementia in the control arm of the trial will die in a carer preferred location, then 408 participants will need to be enrolled in the study to have 90% power to detect a 15% increase in the proportion of people dying in preferred locations to 75%. The Type I error probability associated with these tests of this null hypothesis is 0.05. Applying a small (< 10% tolerance) to incomplete data and loss to follow up, we will enrol 440 participants, 220 per study arm.

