### Outcome measures

The primary outcome measure is the proportion of participants dying in their carer-nominated preferred location for death within 12 months of enrolment. The person-centred secondary outcome measures are changes in carer (proxy) reported and self-ratings of quality of life, symptoms and strain, using the same measurements done at baseline. Other secondary outcome measures will be health system focussed, namely.Number of ED attendances post enrolment (with and without subsequent admission to hospital)Hospital occupied bed days post enrolment, including hospital in the home admissionsDays spent in nominated preferred location of care post enrolmentNumber and type of medical interventions in last seven days of life e.g. IV fluids or antibiotics

Finally, if the person with dementia dies in the follow up period, we will measure bereavement risk in the carer using the Modified Bereavement Risk Index (MBRI) [20].

A recruiter blinded to the allocation arm of the carer will undertake all outcome measure assessments every three months post enrolment, for a maximum of twelve months. Participants will have the choice to enter questionnaire responses directly into an electronic database, or answer questions by phone with the recruiter recording their responses for them.

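### The unconditional 90% power claim rests on an unstated 12-month mortality: the sample size makes no allowance for participants who survive

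*Protocol article*

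**What the plan says.** In the protocol article, Sample size, the control rate is set as follows: "Using this review to assume 60% of people with dementia in the control arm of the trial will die in a carer preferred location". The same section says of the evidence that "only two small studies from a recent systematic review provided data on preferred location of death". It then states that "408 participants will need to be enrolled in the study to have 90% power to detect a 15% increase", to 75%, and on error rates: "The Type I error probability associated with these tests of this null hypothesis is 0.05". The step from 408 to 440 is explained by one phrase: "Applying a small (< 10% tolerance) to incomplete data and loss to follow up".

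Outcome measures defines the primary outcome as "the proportion of participants dying in their carer-nominated preferred location for death within 12 months of enrolment". Its bereavement measure applies only "if the person with dementia dies in the follow up period", so the plan expects some people to be alive when follow-up ends at twelve months. Statistical Analysis specifies intention to treat, with logistic regression for the primary comparison. The article states no 12-month mortality.

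**The concern.** Under the outcome as defined, a participant can fail to be a success in two ways: by dying somewhere else, or by being alive at 12 months. The sample-size calculation appears to model only the first. A survivor with complete follow-up is neither missing nor lost, so the step to 440 is not meant for such people.

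If that reading is right, survivors do one of two things. Kept in the denominator, they shrink both proportions and the difference between them. Left out, they reduce the number analysed. Either way the stated 90% is not what 440 participants deliver. This is the primary outcome, and a non-significant result from a trial with much lower real power would say little about whether the target effect exists.

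**Working it through.** **Inputs.** From Sample size: p1 = 0.60, p2 = 0.75, alpha 0.05, power 90%, 408 before and 440 after inflation. From Randomisation and control arm: 1:1 allocation. Sidedness is not stated; two-sided is used because it reproduces the plan's figure (one-sided gives 332). The share dying within 12 months, d, is not in the document. It is an assumption, varied over a range and taken as equal in both arms.

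**Step 1: reproduce 408.** Two-proportion formula, pooled variance under the null, no continuity correction:

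n per arm = [1.960 × √(2 × p̄ × (1 − p̄)) + 1.2816 × √(p1(1 − p1) + p2(1 − p2))]² / (p2 − p1)²

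With p̄ = 0.675: [1.960 × √0.43875 + 1.2816 × √0.4275]² / 0.0225 = (1.298 + 0.838)² / 0.0225 ≈ 202.8, so 203 per arm, 406 in total. The unpooled version gives 400. At 204 per arm:

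power = Φ{[0.15 × √204 − 1.298] / √0.4275} = Φ(1.291) = 90.2%

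So 408 is reproduced when every one of the 408 contributes an outcome at 60% or 75%. If those are shares of deaths, that means d = 100%.

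**Step 2: the inflation.** 1 − 408/440 = 7.3%, and 408/0.93 = 439, in line with 440. This is also correct.

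**Step 3: let some participants survive.** Take 60% and 75% as shares of deaths.

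- All randomised, survivors as non-events: the proportions become 0.60d and 0.75d, and the difference 0.15d, with n unchanged.
- Decedents only: the proportions stay at 0.60 and 0.75, and n per arm becomes n × d.

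Worked example at d = 0.8, 204 per arm:

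- All randomised, 0.48 vs 0.60: Φ{[0.12 × √204 − 1.960 × √(2 × 0.54 × 0.46)] / √(0.48 × 0.52 + 0.60 × 0.40)} = Φ(0.475) = 68.3%.
- Decedents only, n = 204 × 0.8 = 163.2: Φ{[0.15 × √163.2 − 1.298] / √0.4275} = Φ(0.945) = 82.8%.

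Power at 204 per arm (the plan's allowance fully used), and in brackets at 220 per arm (nobody else lost):

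| d (assumed) | All randomised | Decedents only |
|---|---|---|
| 1.00 | 90.2% (92.2%) | 90.2% (92.2%) |
| 0.95 | 85.4% (87.9%) | 88.7% (90.8%) |
| 0.90 | 80.0% (82.9%) | 86.9% (89.3%) |
| 0.80 | 68.3% (71.5%) | 82.8% (85.5%) |
| 0.70 | 56.6% (59.8%) | 77.5% (80.5%) |
| 0.50 | 36.0% (38.3%) | 63.0% (66.3%) |

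For decedents only, 408 deaths from 440 people means 408/440 = 92.7% mortality. About 93% therefore suffices, but only if nobody is lost for any other reason.

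**Step 4: the other reading.** Suppose 60% and 75% are shares of everyone enrolled. Then 408 stands, but d cannot be below 0.75 in the CELPI arm or 0.60 in the control arm, even if every death is in the preferred place. At d = 0.8 in both arms, the implied shares of deaths are 0.60/0.8 = 75% and 0.75/0.8 = 93.75%.

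**The case against.** The strongest reply is that the sentence giving the 60% speaks of people in the control arm, not of those who die, and that the section opens by naming death within follow-up in the supported location as the outcome. Read literally, mortality is already inside the 60% and 408 is right. What the source review measured cannot be checked from the article. This stands as a possible reading, so it cannot be said as fact that the two rates are shares of deaths. It is the less plausible reading, because the figure comes from location-of-death data. It also does not rescue the unconditional claim, since it needs at least 75% mortality in the CELPI arm, which is not stated either.

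A second reply is that the article condenses a fuller protocol, where a mortality assumption may be given. That is fair, and silence alone would be no finding. What can be criticised is the 90% stated without condition, beside an inflation that names only other losses.

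A third is that the size of the loss is not anchored. That stands. The population has severe dementia, is recruited through an ED visit and is described in the Discussion as nearing the end of life. A reader might infer low mortality from the exclusion of people about to die, but that exclusion covers one week only and says little about twelve months. The document supports no particular d, and the lower rows of the table are illustrations.

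A reader might also infer that 408 or 440 is miscalculated. Neither is; both reproduce.

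**Conclusion.** The concern holds as an unstated assumption behind a stated property of the design. On the more plausible reading, that 60% and 75% are conditional on death, the 90% is delivered only if nearly all participants die within 12 months. Outcome measures and Statistical Analysis point to all randomised as the denominator. There, power is already below 90% at 95% mortality, at 85% (88% with all 440 evaluable), and it falls to 57% (60%) at 70% mortality. With decedents only the loss is milder: 89% (91%) at 95% mortality and 78% (80.5%) at 70%.

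These figures rest on a two-sided 5% test, equal mortality in the two arms and an assumed d. The direction of the shortfall does not depend on d; its size does. It would go too far to say that the trial is underpowered by a known amount, because the article gives no mortality from which to say so.

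**What to change.** In the sample-size section:

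- State that the denominator is all randomised, as the outcome definition and the intention-to-treat analysis imply, or justify a decedents-only analysis.
- State whether 60% and 75% are conditional on death.
- Give the 12-month mortality that 440 relies on.
- Replace the unconditional 90% with power as a function of mortality, and update it from pooled, blinded mortality during recruitment.

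The cost is wording in the protocol and analysis plan, and a less favourable stated power. No extra patients are needed to make the claim accurate.

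Following place of death to a common close-out date is not a way to restore the stated power. It would replace the 12-month outcome with one of unequal follow-up, run past the twelve-month maximum in Outcome measures, and suit the planned logistic regression poorly. It could serve only as a supplementary time-to-event analysis, specified separately.

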### Participant screening and recruitment

There will be a multi-pronged approach to screening and recruitment. A research assistant (the recruiter) working in each of the six EDs will screen electronic records on a daily basis to identify potential people with dementia based on age and available triage information. This will be augmented by direct referrals of potentially eligible patients by hospital clinicians (medical, nursing and allied health) working in the ED. Based on available information, in person or telephone contact will be made with the identified primary carer, where verbal permission will be obtained to continue the screening for inclusion and exclusion criteria with the carer and patient. Once it is determined the patient-carer dyad is eligible for the trial, the carer will be provided with a paper or electronic scanned version (based on their preference) of the trial information and consent form. Signed consent forms will be returned to the recruiter by mail or electronically.

### Baseline assessment

The baseline assessment will be undertaken by the recruiter within seven days of receipt of a signed consent form. This will usually be via telephone with the carer, and will comprise where applicable measures that have undergone prior psychometric validation and are fit for purpose:Carer-informed patient baseline assessmentPast medical history and demographic details, hospitalisations in the prior twelve months. Co-morbidity will be codified using the Charlson Comorbidity Index [12]. Carer information will be confirmed with hospital and other written medical records where available.Australia-modified Karnofsky Performance Status (AKPS) [13].Quality of Life in Late Stage Dementia (QUALID)[14].Symptoms using the Symptom Assessment Scale (SAS) [15]. Although designed to be used by patients to self-report, it has been used for proxy reporting.Preferred location of death. We will capture what was known (if anything) of the preferred location of the person with dementia, but use the carer nominated location for the purpose of the primary outcome adjudication.Carer baseline assessmentDemographic detailsQuality of life (EQ5D) [16].Modified Caregiver Strain Index (MCSI) [17].

### Randomisation and control arm

After baseline assessment by the recruiter, an intervention (CELPI) clinician will be notified by email and will randomly assign participants into one of the two study arms using a web-based randomisation service. This will ensure the recruiter, who will also conduct the three monthly follow up assessments, is blinded to the allocation arm. Randomisation will be in a 1:1 ratio stratified by city of enrolment.

Once randomised, the CELPI clinician, who will have a tertiary degree in a health discipline (e.g. psychology, occupational therapy) but not be a physician, will contact all participants regardless of allocation arm and provide education regarding publicly available resources for the carers of people with dementia. The clinician will have all details of the baseline assessment available to them, such that they will have sufficient information on the person with dementia and their carer, and not need to access hospital records. If in the control arm, the clinician will then have no further contact with the participant. Participants in the control group will receive usual care from all health professionals who are involved in their management during the 12-month follow up. No treatments will be withheld from the control group.

### Intervention arm

The basis of the CELPI intervention is a holistic needs assessment followed by an agreed referral plan to address needs identified by that assessment. Participants will receive at least one visit from the CELPI clinician that will comprise a structured needs assessment using the CANDID tool [18] developed for this trial (Appendix 1). CANDID is designed to capture information on the current and future needs of both the carer and the person with dementia, as well as clarifying what, if any, advance care planning has been done to date. The assessment will be used to develop and implement tailored follow up actions to address these needs mapped to existing available services, but focussing on the two key components of the intervention.

iwhat a palliative care referral would entail; and.iiwhat a palliative approach and advance care planning looks like for a person dying with dementia, stressing at all times that the goal is to align care with the wishes of the person with dementia regarding how they would want their end of life to be. CANDID will capture any prior advance health directive or care plan made by the person with dementia when they had capacity, as well as any prior goals of care discussions already held with the carer.

CELPI will therefore focus on identifying current needs; likely future complications; and if necessary, guiding carer-initiated treatments for distressing symptoms.

CELPI clinicians (one per state) will be currently registered health professionals with experience in the care of people with cognitive impairment and/or palliative care needs, who will receive structured training as members of the research team. This will include education about advanced dementia, the use of CANDID and techniques such as motivational interviewing and goal setting [19]. The competencies and skills of the clinicians will be assessed to ensure fidelity across clinicians and over time through a fidelity checklist developed for the trial (Appendix 2).

The role of the CELPI clinician is not to replace the role of usual treating health care professionals or to provide new services. Instead, the clinician will act as a navigator to help carers understand the CANDID findings, make guided decisions about palliative care and care planning, and develop an action plan for referring and linking the carer into specialist palliative care or dementia services as indicated. This will be supported by the provision of educational materials and a written summary provided to the carer and the GP of the person with dementia. Broadly, reasons for referral to a specialist palliative care service will fall into at least one of three groups: physical symptoms; complex social situations; and anticipated complex grief.

### Outcome measures

The primary outcome measure is the proportion of participants dying in their carer-nominated preferred location for death within 12 months of enrolment. The person-centred secondary outcome measures are changes in carer (proxy) reported and self-ratings of quality of life, symptoms and strain, using the same measurements done at baseline. Other secondary outcome measures will be health system focussed, namely.Number of ED attendances post enrolment (with and without subsequent admission to hospital)Hospital occupied bed days post enrolment, including hospital in the home admissionsDays spent in nominated preferred location of care post enrolmentNumber and type of medical interventions in last seven days of life e.g. IV fluids or antibiotics

Finally, if the person with dementia dies in the follow up period, we will measure bereavement risk in the carer using the Modified Bereavement Risk Index (MBRI) [20].

A recruiter blinded to the allocation arm of the carer will undertake all outcome measure assessments every three months post enrolment, for a maximum of twelve months. Participants will have the choice to enter questionnaire responses directly into an electronic database, or answer questions by phone with the recruiter recording their responses for them.

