### Statistical Analysis

Publication of a full statistical analysis plan separate to this manuscript is planned. This will include details on planned interim and subgroup analyses. Outcome analyses will be undertaken on an intention-to-treat basis by the study statistician blinded to group allocation. The overall difference in proportion of participants dying in a preferred location between the intervention and control groups will be assessed using logistic regression. Secondary outcome analyses of quality of life and strain measures, collected multiple times from the same patient-carer dyad, will be performed by constructing random effects models with the intervention group variable interacted with time to account for within-dyad correlation. Health system outcomes will be assessed by including the intervention group variable in an appropriate count-based regression model that accounts for the variable exposure (length of time before death). Inclusion of baseline data in regression models will be used to explore additional variation within dyad characteristics.

Elements introduced to mitigate bias in the study include use of a computer randomisation service, blinded outcome assessment and intention to treat analysis.

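### The primary outcome counts a participant alive at 12 months as a non-event, so it combines mortality with place of death, and the stated 90% power rests on a 12-month mortality that the protocol does not give

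*Protocol article*

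**What the plan says.** Three sections of the protocol article bear on this.

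- *Outcome measures* defines the primary outcome as "the proportion of participants dying in their carer-nominated preferred location for death within 12 months of enrolment". The same section measures carer bereavement risk only where the person dies during follow-up, so survivors at 12 months are foreseen.
- *Sample size* powers the trial on "the primary outcome of death within the follow up period in the carer supported preferred location". It assumes that "60% of people with dementia in the control arm of the trial will die in a carer preferred location" and that the intervention raises this to 75%. It concludes that "408 participants will need to be enrolled in the study to have 90% power to detect a 15% increase", and enrols 440 to allow for loss.
- *Statistical Analysis* states that "Outcome analyses will be undertaken on an intention-to-treat basis" and that "The overall difference in proportion of participants dying in a preferred location between the intervention and control groups will be assessed using logistic regression". Differing time to death is taken into account only in the count models for health system outcomes.

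The article states no 12-month mortality and no explicit rule for scoring a survivor on the primary outcome.

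**The concern.** A participant is an event only by dying within 12 months and doing so in the nominated place. With every randomised participant in the denominator, someone still alive is coded the same as someone who died where the carer did not want. The outcome therefore has two components:

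P(event) = P(death by 12 months) × P(preferred place | death).

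One logistic regression on the product cannot show which component moved. If mortality differed between arms, the arm with more deaths would score better with place of death unchanged, and the arm with longer survival would score worse even if place of death improved. The trial's question is about the second component.

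The power statement is affected too. Whether 60% and 75% describe all randomised people or only those who die determines what the trial can detect on the endpoint as defined, and the article does not settle it.

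**Working it through.** **Inputs from the article.** Control rate 60%, intervention rate 75%, power 90%, alpha 0.05 (sidedness not stated; two-sided reproduces the figure), 1:1 allocation, 408 before loss (204 per arm), 440 enrolled (220 per arm).

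**Assumed inputs.** All 12-month mortality values, because the article gives none.

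**1. The plan's own figure.** Pooled two-proportion test, mean rate p̄ = 0.675:

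n per arm = [1.96 √(2 × 0.675 × 0.325) + 1.2816 √(0.60 × 0.40 + 0.75 × 0.25)]² / 0.15² = 202.8, so 203 per arm or 406 in total.

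This agrees with 408 (204 per arm gives power 0.902). The arithmetic is sound. The loss allowance is 1 − 408/440 = 7.3%, within the stated limit of 10%.

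**2. Mortality differs, place of death does not.** Preferred place is 60% of deaths in both arms, with 204 analysed per arm, two-sided 5%. With p̄ the mean of the two event rates and d their difference:

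se₀ = √(2p̄(1 − p̄)/204), se₁ = √([p₁(1 − p₁) + p₂(1 − p₂)]/204)

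rejection probability = Φ((d − 1.96 se₀)/se₁) + Φ((−d − 1.96 se₀)/se₁).

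| Mortality, control vs intervention | Event rates | Rejection probability |
|---|---|---|
| 50% vs 50% | 30% vs 30% | 5% |
| 50% vs 55% | 30% vs 33% | 10% |
| 50% vs 60% | 30% vs 36% | 25% |
| 50% vs 65% | 30% vs 39% | 48% |

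For the third row: d = 0.06, se₀ = 0.0466, se₁ = 0.0465, Φ(−0.673) = 0.251. With all 220 per arm analysed, the last two rows become 27% and 51%.

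**3. A real gain offset by longer survival.** Suppose preferred place among deaths truly rises from 60% to 75%. The event rates are equal when 0.60 × m_C = 0.75 × m_I, that is, when m_I/m_C = 0.60/0.75 = 0.80. For example, 0.60 × 0.60 = 0.36 and 0.75 × 0.48 = 0.36.

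**4. What the 90% power requires.**

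(a) *Rates as shares of all randomised.* An event is a death, so at least 60% of controls and 75% of the intervention arm must die within 12 months. At 80% mortality in both arms, the shares of deaths in the preferred place would have to be 0.60/0.80 = 75% and 0.75/0.80 = 94%.

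(b) *Rates among deaths, mortality equal in the two arms.* The event rates shrink to 0.60m and 0.75m. Power at 204 per arm:

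| Mortality m | Event rates | Power |
|---|---|---|
| 90% | 54% vs 67.5% | 80% |
| 80% | 48% vs 60% | 68% |
| 60% | 36% vs 45% | 46% |
| 50% | 30% vs 37.5% | 36% |

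(c) *Analysis confined to deaths.* At 60% mortality, 408 × 0.60 ≈ 245 people are analysed and power for 60% vs 75% is about 71%. At 50% mortality with all 440 followed, 220 are analysed and power is about 66%.

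**The case against.** **Survivor scoring is inferred.** No sentence says that survivors are failures. It follows from the definition over participants, the rates given for whole arms and the intention-to-treat analysis. A separate analysis plan is announced and may add a survivor rule or supplementary analyses. This stands as a limit on certainty. It does not remove the point, because the article itself already fixes the outcome, the analysis set and the method.

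**There is no evidence of a survival effect.** A reader might infer that the primary result will be distorted. The article does not support that. The clinician is a navigator who adds no new services, contact may be a single visit, and nothing is withheld from controls. If true mortality is the same in both arms, the test keeps its 5% level. Cancelling the full gain needs a 20% relative reduction in mortality, which is large, and a 5-point mortality difference raises rejection only to about 10%. Even where mortality differs, the defined endpoint really does differ, and the test is valid for it and preserves randomisation. The difficulty is one of interpretation.

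**The 60% may not be a share of deaths.** A reader might infer that the sample-size assumption concerns deaths only and so contradicts the outcome definition. Its origin in studies of preferred place of death favours that reading, but the wording refers to people in the control arm and is applied to the number enrolled. Both readings are open.

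**A deaths-only primary analysis looks like the natural cure.** It is a trade-off. It conditions on a post-randomisation event, so it loses the protection of randomisation in exactly the case where survival differs, and it has less than the stated power (step 4c). Nor would it help to allow a claim of benefit only if deaths elsewhere fall. With preferred place fixed at 60%, mortality of 60% versus 50% alone lowers deaths elsewhere from 0.40 × 0.60 = 24% to 0.40 × 0.50 = 20%.

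**Conclusion.** The point holds as one of definition, interpretation and stated power. The outcome as written is a composite of dying within 12 months and dying in the nominated place. A difference on it can be read as a change in place of death only when mortality by arm is shown beside it. How far mortality could move it depends wholly on assumed values: about 10%, 25% or 48% rejection for differences of 5, 10 or 15 points from a base of 50%, with place of death unchanged.

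The 408 is correctly calculated. The 90% power applies to this endpoint only if 60% and 75% are shares of all randomised, which implies at least 60% and 75% mortality in the respective arms. If they are shares of deaths, power is about 68% at 80% mortality, 46% at 60% and 36% at 50%, assuming equal mortality. The article does not show which case applies, and it does not show that the intervention alters survival.

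**What to change.** 1. Keep the intention-to-treat endpoint as primary, and state that a participant alive at 12 months is a non-event.
2. Pre-specify beside it, in all randomised and by arm, 12-month status in three categories (died in the nominated place, died elsewhere, alive). Add cumulative incidence of death in the nominated place with death elsewhere as a competing event, and the mortality difference with its confidence interval.
3. Add place of death among those who died as a supporting analysis, labelled as conditioning on a post-randomisation event.
4. State that the primary result will be interpreted as improved place of death only in the light of items 2 and 3. Do not make a fall in deaths elsewhere a formal condition.
5. In *Sample size*, say whether 60% and 75% refer to all randomised or to deaths, give the assumed 12-month mortality, and restate the power accordingly. No increase in enrolment is proposed.

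Cost: wording in the protocol and analysis plan, a little more analysis, and possibly a less favourable stated power. Little new data should be needed, since place of death serves the primary outcome and time to death serves the planned count models.
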